**Secondary:**

- Time to a normal body temperature [ Time Frame: From the time of randomization until the time of normal body temperature, assessed up to 15 days]
- Time to the alleviation of nasal/throat/chest symptoms [ Time Frame: From the time of randomization until the time of absence of nasal/throat/chest symptoms, assessed up to 15 days
- Proportion of participants in each group with normalization of fever [ Time Frame: day 7 and day 15 ]
- Proportion of participants in each group with oxygen saturation > 94% on room air for >24h [ Time Frame: day 7 and day 15 ]
- Time to fever normalization (if febrile at baseline) [ Time Frame: within 15 days ]
- Time to first negative SARS-CoV-2 PCR in NP swap (if pos. at baseline) [ Time Frame: within 15 days ]
- Time to first negative SARS-CoV-2 PCR in lower respiratory tract specimens (sputum, bronchoalveolar lavage, tracheal aspirate) (if positive at baseline) [ Time Frame: within 15 days ]
- Duration of oxygen therapy [ Time Frame: within 30 days ]
- Proportion of participants in each group with need for mechanical ventilation [ Time Frame: within 30 days ]
- Duration of hospitalization [ Time Frame: within 28 days ]
- All cause mortality [ Time Frame: day 30 ]

**Study Center(s):** Study in Indian population and recruitment will happen up to 5 research sites based on competitive patient recruitment.

**Phase of Development:** Proof of Concept/ Intervention Trial on traditional medical product.

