**Primary Efficacy Endpoint:**

The Odds of Ratio for Improvement on a 7-point Ordinal Scale on Day 15 [Time Frame: Day 15 from the day of study inclusion]. The odds ratio represents the odds of improvement in the ordinal scale between the treatment groups. The ordinal scale is an assessment of the clinical status at a given day. Each day, the worst score from the previous day will be recorded.

The scale is as follows: 1. Death 2. Hospitalized, on invasive mechanical ventilation or Extracorporeal Membrane Oxygenation (ECMO) 3. Hospitalized, on non-invasive ventilation or high flow oxygen devices 4. Hospitalized, requiring low flow supplemental oxygen 5. Hospitalized, not requiring supplemental oxygen - requiring ongoing medical care (Coronavirus (COVID-19) related or otherwise) 6. Hospitalized, not requiring supplemental oxygen - no longer required ongoing medical care (other than per protocol ZingiVir-H administration) 7. Discharge from hospital.

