**Statistical Methods:**

The total sample size is 112 randomized subjects. This sample size is allocated to treatment arms in a 1 to 1 ratio. This sample size provides 50% power if the following assumptions are made based on earlier reviews. SAS 9.4 statistical analysis software will be used for statistical analyses. T-test will be used for comparisons between groups for continuous variables. The comparison between groups for categorical variables will be performed using Fisher's exact probability method. Means and standard deviations will be used to describe centralized discrete trends. The t-test, rank-sum test, and Fisher's exact probability method will be used for comparisons between groups. P 0.05 indicates that the difference was statistically significant.

**RANDOMIZED CONTROLLED SINGLE BLINDED PROSPECTIVE MULTI CENTRE CLINICAL TRIAL TO INVESTIGATE THE SAFETY AND EFFICACY OF ZINGIVIR-H AS AN ADJUVANT THERAPY IN HOSPITALIZED ADULTS DIAGNOSED WITH CORONAVIRUS DISEASE 2019 (COVID-19).**

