**INVESTIGATIONAL PLAN**

**Overall Study Design**

This is a Randomized controlled, single blinded multi-center, comparative study of ZingiVir-H as an adjuvant therapy in hospitalized adults diagnosed with coronavirus disease 2019 (COVID-19). At inclusion, subjects who meet all inclusion criteria and no exclusion criteria will be assigned, in either therapeutic arm (ZingiVir-H), to receive ZingiVir-H in a dose of 500 mg tablet each consumed once in 3 hours ±1 hour between 6 AM and 9 PM in a given day (6AM, 9AM, 12Noon, 3PM, 6PM, 9PM) for a minimum duration of 10 days to Maximum 15 days OR will be on a Placebo arm to receive placebo (without active ingredients) each consumed once in 3 hours ±1 hour between 6 AM and 9 PM in a given day (6AM, 9AM, 12Noon, 3PM, 6PM, 9PM) for a minimum duration of 10 days to Maximum 15 days. The allocation of study arm is strictly as per the discretion of the Investigator. Whereas both the study groups shall be given standard of care of treatment as per the research site policies or COVID-19 therapeutic management policies. These doses will be administered orally. Blood samples for assessing CBC; safety laboratory tests and immunomodulatory markers will be obtained between baseline assessments (Day-01), during the day-06 of inclusion, at the end of the treatment day-15 and at the end of the study day-30. Safety-related assessments will include reports of adverse events and clinical laboratory test results.

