**Visit Schedule and Assessments**

**Screening / Randomization Visit – Day 01**

Subjects must meet the inclusion criteria and have none of the exclusion criteria in order to be eligible for randomization in this study. Subjects who meet all eligibility criteria, and have signed informed consent will be discussed randomize and move on to the Baseline study visit. Once the subject is randomized the sponsor representative or the study Investigator will provide the study staff with a unique randomization number for the subject.

Following assessments must be made at this Baseline visit for each study subject:

- RT-PCR test assuring the subjects test positive for COVID-19.
- Demographics
- Medical history (all known information regarding the subject’s health history/relevant surgeries/interventions prior to signing the informed consent).
- Vital signs: Body temperature, Pulse – beats per minute (BPM), Blood Pressure (BP) mmHg, Respirations – breaths per
- Concomitant medications (including medications, fluids and blood products administered within the 7 days prior to randomization).
- Documentation of any other infection if available (site of infection and, if available: positive culture results, prior antibiotics, sensitivity of cultured organism to antibiotics, nonmedical treatment such as surgery or drainage).
- Physical Examination including the following: general appearance, Head, Eye, Ear Nose Throat (HEENT), neck, respiratory, cardiovascular, chest, abdomen, lymphatic, musculoskeletal and extremities, skin and neurologic examination. Height and weight (baseline dry weight).
- Blood will be obtained for following laboratory tests:
  - Complete Blood Count with differential (Hemoglobin, Hematocrit, and WBC with differential count) & ESR
  - Serum Chemistry- Creatinine, Urea, CRP, ALT, AST, Alkaline Phosphatase, Albumin, total bilirubin
  - Pregnancy test; Serum or Urine human Chorionic Gonadotropin (hCG) - Pregnancy test only required for woman of childbearing potential on the day of randomization
  - Immunomodulatory markers, IL6, IL7, Interferon α, IgG, IgM

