**Data Management**

**Documentation**

Case report forms (CRFs) will identify each subject by subject number (compilation of site number and randomization number) and subject's initials (per local regulatory guidelines). Originals or copies of all source documents, and correspondence will be kept on file at the investigational site.

The data required by the protocol will be recorded in the appropriate pages of CRFs. All source data will be available to the study monitor who may perform a 100% data check (comparison of the data recorded in the eCRF with those in the source documents). The source data will also be available for an audit by the Sponsor and all applicable regulatory agencies at any time.

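### Care and discharge practice can differ by site, yet the only stated allocation rule is 1:1 for the whole sample; stratifying by site would be a cheap improvement

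*Protocol*

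**What the plan says.** **Background care.** Overall Study Design states: "Whereas both the study groups shall be given standard of care of treatment as per the research site policies or COVID-19 therapeutic management policies". Care is the same in kind for both arms but may differ between sites.

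**Sites.** The Protocol Synopsis, Study Center(s), says that "recruitment will happen up to 5 research sites based on competitive patient recruitment". Site sizes are therefore not fixed in advance.

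**Allocation.** The Synopsis, Statistical Methods, says of the 112 subjects: "This sample size is allocated to treatment arms in a 1 to 1 ratio". The Screening / Randomization Visit section adds only that "the sponsor representative or the study Investigator will provide the study staff with a unique randomization number for the subject". Strata, blocks and site lists are not described. Under Data Management, Documentation, each subject is identified by a "subject number (compilation of site number and randomization number").

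**A conflicting sentence.** Just before the sentence on background care, Overall Study Design says: "The allocation of study arm is strictly as per the discretion of the Investigator".

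**Endpoint and tests.** The primary endpoint is "The Odds of Ratio for Improvement on a 7-point Ordinal Scale on Day 15". Category 5 is in hospital without oxygen but still needing care, category 6 is in hospital with that need ended, and category 7 is discharge. Statistical Methods names the t-test, the rank-sum test and Fisher's exact test.

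**The concern.** Entrants must be in hospital, need care for COVID-19 and have an oxygen saturation above 94% without supplemental oxygen. Most would therefore start at category 5 (an inference; the protocol gives no baseline distribution). From there, improvement means that a clinician judges care no longer necessary or sends the patient home. Local policy can move both decisions without any drug effect.

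Site is thus a foreseeable non-drug influence on the primary odds ratio. If the 1:1 ratio is held only over the whole sample, one arm can by chance draw more patients from a site that discharges early, and the crude odds ratio then carries part of the site difference. Balance by site has to be arranged before the first patient enters. An analysis can adjust for site later but cannot restore the balance.

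**Working it through.** **1. The plan's own figure.** 100 evaluable subjects with 10% drop-out: 100 / 0.90 = 111.1, rounded up to 112. This reproduces, and 1:1 gives 56 per arm. The stated 50% power cannot be checked, because the assumptions announced with it are not given.

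**2. Chance of imbalance at one site.** Inputs: 112 subjects and 56 per arm (protocol); 40 subjects at one site (assumption). If only the overall ratio is held, the number X of those 40 who receive the study drug is hypergeometric:

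P(X = k) = C(40, k) × C(72, 56 − k) / C(112, 56), with mean 40 × 56/112 = 20.

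| Split at the site, or worse | Either direction | Towards the drug arm |
|---|---|---|
| 23:17 | 32% | 16% |
| 24:16 | 17% | 8.4% |
| 25:15 | 7.5% | 3.8% |
| 26:14 | 2.9% | 1.5% |

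**3. Effect on the odds ratio with no drug effect.** Let p be the Day 15 improvement rate at that site and q the rate elsewhere. Neither is in the protocol, so three contrasts are assumed. With a k:(40 − k) split, expected improvers are A = k·p + (56 − k)·q in the drug arm and B = (40 − k)·p + (16 + k)·q in the placebo arm. The apparent odds ratio is [A/(56 − A)] / [B/(56 − B)].

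For 24:16:
- 75% v 65%: A = 18.0 + 20.8 = 38.8; B = 12.0 + 26.0 = 38.0; (38.8/17.2)/(38.0/18.0) = 1.07.
- 80% v 60%: A = 19.2 + 19.2 = 38.4; B = 12.8 + 24.0 = 36.8; (38.4/17.6)/(36.8/19.2) = 1.14.
- 90% v 50%: A = 21.6 + 16.0 = 37.6; B = 14.4 + 20.0 = 34.4; (37.6/18.4)/(34.4/21.6) = 1.28.

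At the widest contrast, 25:15 gives (38.0/18.0)/(34.0/22.0) = 1.37 and 26:14 gives (38.4/17.6)/(33.6/22.4) = 1.45. A split the other way gives the reciprocals.

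**4. Five sites.** This is a simulation with no drug effect, using 6,000 allocations per setting. Assumed improvement rates by site are 0.80/0.70/0.60/0.50/0.40 (moderate) or 0.90/0.80/0.50/0.30/0.20 (wide). Assumed sizes are 23/23/22/22/22 (equal) or 45/30/20/10/7 (unequal). The middle columns give the central 95% of odds ratios produced by site mix alone.

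| Spread, sizes | 1:1 overall only | Blocks of 4 within site | Beyond 1.25-fold, overall only |
|---|---|---|---|
| Moderate, equal | 0.81–1.24 | 0.95–1.05 | 4% |
| Moderate, unequal | 0.81–1.22 | 0.94–1.07 | 4% |
| Wide, equal | 0.67–1.51 | 0.91–1.10 | 29% |
| Wide, unequal | 0.67–1.50 | 0.88–1.14 | 30% |

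With blocks within site, no allocation went beyond 1.25-fold. The median largest within-site difference between arms fell from 6 patients to 2.

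**5. Bias and type I error.** The mean log odds ratio was about 0 in every setting. With 1:1 overall only, Fisher's test (2,500 of the allocations, two-sided 0.05) rejected in 2.5% to 3.2%. With blocks within site and the wide spread, the same unstratified test rejected in only 1.1%. Stratified allocation analysed without site is conservative, so the two changes belong together.

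**6. Scale.** In the 90% v 50% case, overall improvement is (36 + 36)/112 = 64%. Ordinary sampling error is then SE(log OR) = √[2/(56 × 0.643 × 0.357)] = 0.39, a 95% factor of exp(1.96 × 0.39), about 2.2. Site mix adds to that but does not dominate it.

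**The case against.** Unstratified randomization is a valid design, and site-determined background care is normal in an add-on trial because it applies to both arms. A reader might infer that the site differences bias the odds ratio or inflate false positives. The documents do not support that: if allocation is truly random, chance imbalance averages out, and the rejection rates above stay below 5%. What remains is lost precision and possible imbalance in the single trial that is run. With moderate site differences that is small beside sampling error.

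A reader might also infer that the trial is definitely unstratified. The protocol is silent rather than explicit, and a subject number built from site and randomization numbers is compatible with lists kept per site, though it does not establish them. A site term may sit in a statistical analysis plan that is not shown, so its absence from Statistical Methods is not a fault in itself. Stratified allocation is different, since it has to be settled before enrolment.

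The strongest objection is that the sentence giving allocation to the investigator undercuts every probability above. If it were followed, imbalance would not be due to chance and could be systematic, and site lists would cure nothing. That is a separate and graver contradiction with randomization. It stands, and it has to be removed first.

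**Conclusion.** The point holds as a cheap improvement. Site can plausibly influence a primary endpoint driven by care and discharge decisions, and the only stated allocation rule does not balance it. The consequence is avoidable noise and possible imbalance by site, without average bias or type I inflation. With 40 patients at one site, the 17% event of a 24:16 split or worse starts at an apparent odds ratio of 1.07 to 1.28 (or the reciprocal), depending on the contrast between sites. Over five sites, site mix alone spans about 0.81 to 1.24 (moderate) or 0.67 to 1.51 (wide).

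The full change gains little power. A simulation with the same kind of assumed site rates and a true odds ratio of 2.2 gave 38% rising to 40% (moderate) and 27% rising to 33% (wide); the exact gain depends on the tests compared.

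Site sizes and site improvement rates are assumptions throughout, and the calculations presuppose genuine randomization with 56 per arm.

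**What to change.** 1. In Overall Study Design, delete the sentence that leaves the arm to the investigator's discretion. The other steps have no value while it stands.
2. In Statistical Methods and in the Screening / Randomization Visit section, state that 1:1 randomization is concealed, centrally held and stratified by site, in randomly varying block sizes so that the next assignment cannot be guessed.
3. State that the primary odds ratio is estimated with site as a stratum, with very small sites pooled by a rule set in advance.

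The cost is up to five lists instead of one and a stratum term in the analysis, with no extra patients. Incomplete last blocks may leave a minor overall imbalance, and stratification reduces site imbalance without removing it entirely (0.88 to 1.14 in the least favourable setting above).

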**Study Objectives**

**Primary:**

- The primary objective of this study is to evaluate the efficacy of ZingiVir-H regimens and standard of care compared to placebo and standard of care (SOC), with respect to clinical status assessed based on patient diary data and based on Ordinal scale on the ration of Improvement. [Time Frame: From the time of randomization until the time of alleviation of all symptoms, assessed up to the test results shows negative]
- To determine the safety of ZingiVir-H in this test population.

**Secondary:**

- Time to a normal body temperature [ Time Frame: From the time of randomization until the time of normal body temperature, assessed up to 15 days]
- Time to the alleviation of nasal/throat/chest symptoms [ Time Frame: From the time of randomization until the time of absence of nasal/throat/chest symptoms, assessed up to 15 days
- Proportion of participants in each group with normalization of fever [ Time Frame: day 7 and day 15 ]
- Proportion of participants in each group with oxygen saturation > 94% on room air for >24h [ Time Frame: day 7 and day 15 ]
- Time to fever normalization (if febrile at baseline) [ Time Frame: within 15 days ]
- Time to first negative SARS-CoV-2 PCR in NP swap (if pos. at baseline) [ Time Frame: within 15 days ]
- Time to first negative SARS-CoV-2 PCR in lower respiratory tract specimens (sputum, bronchoalveolar lavage, tracheal aspirate) (if positive at baseline) [ Time Frame: within 15 days ]
- Duration of oxygen therapy [ Time Frame: within 30 days ]
- Proportion of participants in each group with need for mechanical ventilation [ Time Frame: within 30 days ]
- Duration of hospitalization [ Time Frame: within 28 days ]
- All cause mortality [ Time Frame: day 30 ]

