**Secondary Efficacy Endpoint:**

- Proportion of Participants experiencing Treatment-Emergent Adverse Events [Time Frame: First dose date up to 15 days]
- Changes in Haematological and Biochemical parameter like CBC,ESR, CRP, Troponin, Liver function test, Renal function test, [Time Frame: First dose date up to 15 days]
- Changes in inflammatory markers - IL2, IL6, Interferon α, IgG, IgM
- Significant changes in the Chest X-Ray before and after treatment.

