**Subject Eligibility Criteria**

**Inclusion Criteria**

This study targets infectious subjects normally associated with treatment in hospital setting. The following main criteria for inclusion must be met for study entry:

1. Patients of both sexes aged from 18 years to 60 years old.
2. Willing and able to provide written informed consent prior to performing study procedures by the subject or legal guardian willing and able to provide written informed consent prior to performing study procedures
3. Patients with Severe Acute Respiratory Syndrome Coronavirus (SARS-CoV)-2 infection confirmed by RT Polymerase chain reaction (RT-PCR) test between 1 and 120 Hours before randomization
4. Currently hospitalized and requiring medical care for COVID-19
5. Peripheral capillary oxygen saturation (SpO2) > 94% on room air at screening
6. Radiographic evidence of pulmonary infiltrates

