**Laboratory Samples**

Hospital laboratory can be used to access the following test. If the hospital laboratory has limitation an outside laboratory with NABL accreditations shall be arranged for sample analysis.

- Complete Blood Count with differential (Hemoglobin, Hematocrit, and WBC with differential count) & ESR – **Day-01, 06, EOT (Day15) & 30 of study period**
- Serum Chemistry- Creatinine, Urea, CRP, ALT, AST, Alkaline Phosphatase, Albumin, total bilirubin- **Day-01, Day 06 Only CRP, End of treatment- Day 10 OR Day 15, & End of study period Day 30**.
- Pregnancy test; Serum or Urine human Chorionic Gonadotropin (hCG) - Pregnancy test only required for woman of childbearing potential on the day of randomization (**Day-01**).
- Immunomodulatory markers, IL6, IL7, Interferon α, IgG, IgM- **Day 01, Day 06, End of treatment- Day 10 OR Day 15, & End of study period Day 30**.

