**Dosing Visits - Day-1 to EOT (Day15)**

The first dose of study drug must be swallowed within 4 hours from the time study inclusion. The study drug shall be continuing daily each consumed once in 3 hours ±1 hour between 6 AM and 9 PM in a given day (6AM, 9AM, 12Noon, 3PM, 6PM, 9PM) for a minimum duration of 10 days to Maximum 15 days whereas the daily dose shall be administered orally once in 4 ±2 hours interval ie 6 tablets per day.

Following the administration of the first dose record the following:

- Changes in concomitant medications
- Adverse Events/Serious Adverse Events
- Major respiratory failure Events
- Interventions or Surgeries
- Vital signs

**Routine assessment visit and Study drug compliance** – Day 2 to EOT (Day 15)

Following assessments must be made on daily basis for each study subject:

- Vital signs: Pulse – Body temperature, beats per minute (BPM), Blood Pressure (BP) mmHg, Respirations – breaths per minute
- Concomitant medications (including medications, fluids and blood products administered within the 7 days prior to randomization).
- Documentation of any adverse events
- Blood will be obtained for following laboratory tests – only on **Day 06**
  - Complete Blood Count with differential (Hemoglobin, Hematocrit, and WBC with differential count)
  - Serum Chemistry ESR, CRP
  - Immunomodulatory markers, IL6, IL7, Interferon α, IgG, IgM

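### Several secondary endpoints do not match the protocol's own entry criteria, visit lists and assay lists

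*Protocol*

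**What the plan says.** **Oxygen saturation.** The secondary objectives include "Proportion of participants in each group with oxygen saturation > 94% on room air for >24h", at day 7 and day 15. The Inclusion Criteria require "Peripheral capillary oxygen saturation (SpO2) > 94% on room air at screening". The daily list from Day 2 to end of treatment reads "Vital signs: Pulse – Body temperature, beats per minute (BPM), Blood Pressure (BP) mmHg, Respirations – breaths per minute". SpO2 is not in it, nor in the itemised vital signs at baseline and at the end-of-treatment visit. The first-dose and Day 30 lists name vital signs without itemising them.

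**PCR.** Two secondary outcomes are the time to a first negative SARS-CoV-2 PCR within 15 days, one by nasopharyngeal swab and one by lower respiratory tract specimen. Under Visit Schedule and Assessments, RT-PCR appears once, at Day 01, with no specimen type.

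**Imaging, troponin and markers.** The Synopsis, under Secondary Efficacy Endpoint, lists "Significant changes in the Chest X-Ray before and after treatment", change in troponin, and "Changes in inflammatory markers - IL2, IL6, Interferon α, IgG, IgM". Laboratory Samples lists "Immunomodulatory markers, IL6, IL7, Interferon α, IgG, IgM", and each visit that draws markers repeats that set. No laboratory or visit list contains a chest X-ray or troponin.

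**Fever.** There are three overlapping outcomes: the time to a normal temperature, "Proportion of participants in each group with normalization of fever" at day 7 and day 15, and the time to fever normalization. Only the last is limited to patients febrile at baseline. Fever is not an entry criterion.

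**Two lists.** The secondary objectives and the Secondary Efficacy Endpoint list share no item.

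**The concern.** An endpoint needs a scheduled measurement and a population in which it can change. A site that follows the visit lists exactly would finish the trial with no IL2 or troponin values, no PCR after baseline, no follow-up X-ray and no protocol-driven SpO2 readings. A statistical analysis plan cannot restore measurements that were never taken.

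The gaps could be filled from tests ordered in routine care. The timing of those tests would follow illness and discharge, which may differ between arms, and a first negative PCR found that way depends on when someone chose to test.

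The SpO2 and fever outcomes raise a further question of meaning. If most patients meet the success condition on entry, a small observed difference says little about recovery.

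**Working it through.** **Step 1: the plan's own figure.** The evaluable number is 100 with 10% drop-out: 100 / (1 − 0.10) = 111.1, rounded up to 112, as stated. With 1:1 allocation this gives 50 evaluable patients per arm, used below. The stated 50% power cannot be reproduced, because the protocol gives no effect size or event rate.

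**Step 2: each endpoint against the schedule.**

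| Endpoint | Scheduled after baseline? | Consequence |
|---|---|---|
| SpO2 above 94% for more than 24 h, day 7 and 15 | Not in any itemised list | No protocol-driven readings |
| Time to negative nasopharyngeal PCR | No; Day 01 only | Cannot be derived from scheduled tests |
| Time to negative lower-tract PCR | No; specimen in no visit list | As above, and baseline status unknown |
| Chest X-ray change | No; infiltrates appear only as an entry requirement | No scheduled after-treatment film |
| Troponin change | No; not at baseline either | No values |
| IL2 change | No; IL7 is assayed | No IL2 values, and IL7 serves no endpoint |
| Fever outcomes | Yes; temperature is recorded daily | Measurable, but two have no baseline restriction |

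**Step 3: size of the SpO2 ceiling.** The Synopsis (Statistical Methods) names Fisher's exact test for categorical variables and a 0.05 level; I take it as two-sided. Power is the sum, over all success counts a and b out of 50, of Bin(a; 50, p₁) × Bin(b; 50, p₂), counting only the tables with Fisher p ≤ 0.05. The protocol gives no rates, so all of those below are assumptions.

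| Control | Treated | Exact Fisher power |
|---|---|---|
| 80% | 98% | 78% |
| 85% | 98% | 51% |
| 90% | 98% | 19% |
| 90% | 96% | 9% |
| 95% | 98% | 1.5% |
| 90% | 100% | 38% |
| 95% | 100% | 4% |
| 90% | 70% (harm) | 64% |

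For scale: with no failures among 50 treated patients, 5 of 50 control failures give p = 0.056 and 6 of 50 give p = 0.027. At least 12% of controls must therefore fail before even a perfect treated arm reaches significance.

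**Step 4: fever dilution.** Let f be the share febrile at baseline, and let r_C and r_T be the normalization rates among febrile patients. If afebrile patients count as normal, the proportions are 1 − f(1 − r_C) and 1 − f(1 − r_T), and their difference is f(r_T − r_C). With assumed rates of 60% and 85% the difference is 0.25f:

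- f = 1: 25 points
- f = 0.75: 18.8 points
- f = 0.5: 12.5 points
- f = 0.25: 6.3 points

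Restriction corrects the estimate more than the power. At f = 0.5, exact Fisher power is 33% for 80% v 92.5% with all 50 per arm, and 38% for 60% v 85% with the 25 febrile per arm.

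**The case against.** The strongest reply is that a reader might infer from these gaps that the endpoints cannot be answered at all. The documents do not support that across the board:

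- **PCR is scheduled, but only at baseline.** The time frame of the primary objective runs until tests turn negative, so repeat testing is evidently intended. What is missing is when it happens. This stands, and the point is limited to PCR after baseline.
- **The SpO2 outcome has a meaning.** Entry rests on one screening reading, patients can deteriorate, and levels 2 to 4 of the ordinal scale provide for it. Maintenance is a legitimate outcome. A reader might infer that it would show no difference whatever the drug does, but step 3 shows that large benefits or harms are detectable. The missing measurement is the more serious defect.
- **One fever outcome is properly restricted**, and daily temperatures make it answerable. Normalization of fever can also be read as presupposing fever. The protocol does not say how afebrile patients are scored, so the dilution in step 4 is conditional.
- **Some of this could be settled in a statistical analysis plan**, such as the population for each symptom outcome. That is fair for fever. It does not help where no measurement is scheduled or where the endpoint and the assay name different interleukins.
- **Objectives and efficacy endpoints are different headings**, so the lists need not be identical. Even so, they share no item, and the reader cannot tell which one governs.

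**Conclusion.** The point holds as a mismatch between the secondary endpoints and the protocol's own entry criteria, visit lists and assay lists. The text alone establishes these items: no itemised SpO2 after screening, no PCR after baseline, no lower-tract specimen, X-ray or troponin in any list, IL2 against IL7, a shared SpO2 cut-off, two unrestricted fever outcomes of three, and two different secondary lists.

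The size of the SpO2 ceiling depends on assumed rates. In the benefit scenarios with 98% on treatment, power runs from 1.5% to 78% as the control rate falls from 95% to 80%. The fever dilution is proportional to the share febrile and holds only if afebrile patients count as normal.

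Only secondary endpoints are affected, so this should be corrected but does not by itself undermine the Day 15 ordinal-scale endpoint.

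**What to change.** - **SpO2:** add it to the daily vital signs, and restate the outcome as the proportion with any SpO2 of 94% or below, or any supplemental oxygen, by Day 15. This states plainly that deterioration is being measured. It may collect more events by accumulating over time, but it overlaps the ordinal scale and the oxygen-duration outcome and is not shown to remove the ceiling.
- **PCR:** schedule nasopharyngeal tests on the same fixed days in both arms and analyse the proportion negative on those days, or delete the PCR outcomes. Two sampling days, such as Day 6 and Day 15, would be too coarse for a time to first negative.
- **Lower-tract PCR, chest X-ray and troponin:** delete unless scheduled at baseline and Day 15.
- **Interleukin:** make the endpoint and the assay lists name the same one.
- **Fever:** limit the outcomes to patients febrile at baseline and delete the duplicate time-to-event outcome.
- **Lists:** keep one secondary list.

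The cost is amendment wording, bedside SpO2 readings and any tests added to the schedule. Some endpoints are dropped or become fixed-day proportions, and the restricted fever outcomes use fewer patients.

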**Study Period:**

Estimated time of first subject enrollment: 1 Q 2020

Estimated time of last subject enrollment: 1Q 2020

Number of Subjects (planned): Approximately 112 randomized subjects with assumed drop-outs of 10%; 100 evaluable subjects.

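### Length of hospital stay is a plain duration with no place for death, so an early in-hospital death scores like an early discharge; oxygen duration shares the flaw, but with no fixed direction

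*Protocol*

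**What the plan says.** The secondary objectives appear twice, in the Protocol Synopsis and again under Study Objectives. Both lists include "Duration of hospitalization [ Time Frame: within 28 days" and "Duration of oxygen therapy [ Time Frame: within 30 days", and neither adds a definition beyond the window. Mortality is a separate item in the same lists, "All cause mortality [ Time Frame: day 30", and is not linked to the durations.

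The Statistical Methods section of the synopsis states "T-test will be used for comparisons between groups for continuous variables". It also names the rank-sum test and Fisher's exact test.

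The primary endpoint does give death a place. Its seven-point scale opens with "The scale is as follows: 1. Death 2. Hospitalized, on invasive mechanical ventilation or Extracorporeal Membrane Oxygenation (ECMO" and ends with discharge at 7, so death is the worst state and discharge the best.

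The section on discontinuation covers stopping study drug and documenting withdrawal or loss to follow-up. It does not say how a death enters the durations.

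**The concern.** A duration compared by its mean or its rank treats shorter as better. For hospital stay that is sensible only if the stay ends in discharge. A stay can also end in death, and then a short stay is the worst outcome. If death simply stops the clock, the variable gives one value to two outcomes that the trial's own primary scale ranks furthest apart.

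The rank-sum test does not cure this, because an early death still receives the rank of a short stay. The fault is in the variable rather than the test.

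At stake is the reading of a secondary efficacy comparison in a trial that also has safety as a primary objective. If one arm had more early deaths, its mean stay would be pulled down, and the stay comparison would point towards the arm with the worse survival.

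**Working it through.** **Inputs from the protocol**

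- Sample size: "Approximately 112 randomized subjects with assumed drop-outs of 10%; 100 evaluable subjects". Check: 100/(1 − 0.10) = 111.1, rounded up to 112, so the stated figure is reproduced.
- Allocation: "This sample size is allocated to treatment arms in a 1 to 1 ratio", hence 100/2 = 50 evaluable per arm.
- Windows: 28 days for stay, 30 days for oxygen.
- Deaths: no expected number is given. The Background section's crude ratios of deaths to cases are 103,803/1,714,782 = 6.1% worldwide, and 166/5,734 = 2.9% and 242/6,634 = 3.6% for India. Applied to 112 patients they give about 3 to 7 deaths. They are not specific to this population.

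**Inputs assumed**

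The protocol gives no mean or SD for stay or oxygen use. Its power statement, "This sample size provides 50% power if the following assumptions are made based on earlier reviews", is not followed by any assumptions. I take a survivor mean stay of 14 days (range 10 to 18) and death on Day 5.

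**Hospital stay**

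If *e* extra patients in an arm of *n* = 50 die on day *d* instead of surviving with mean stay *m*, the arm mean shifts by *e*(*d* − *m*)/*n*. If death is scored as 28, the shift is *e*(28 − *m*)/*n*.

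- One death, *m* = 14: (5 − 14)/50 = −0.18 day.
- Three deaths, *m* = 14: 3 × (5 − 14)/50 = −0.54 day; scored as 28, 3 × (28 − 14)/50 = +0.84 day.

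| Survivor mean stay (assumed) | One Day-5 death, raw | Three, raw | Three, death scored 28 |
|---|---|---|---|
| 10 days | −0.10 | −0.30 | +1.08 |
| 14 days | −0.18 | −0.54 | +0.84 |
| 18 days | −0.26 | −0.78 | +0.60 |

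The sign reverses across the whole range. The formula also shows the limit: only a death earlier than the survivors' mean stay lowers the arm mean. A Day-20 death with *m* = 14 raises it by (20 − 14)/50 = 0.12 day, though by less than the (28 − 14)/50 = 0.28 day under worst-value scoring.

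**Effect on the t-test**

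This is a simulation with 20,000 runs and 50 per arm. Survivor stay has mean 14 and SD 5, deaths fall on Days 2 to 8, and there is no true effect on stay. All of these are assumptions. The last two columns give the chance of a significant result favouring the arm with more deaths; the nominal value is 2.5%, and the simulation returns 2.5% when nobody dies.

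| Mortality, control vs active | Mean difference, raw | Mean difference, death = 28 | Wrong-way significance, raw | Wrong-way significance, death = 28 |
|---|---|---|---|---|
| 3% vs 6% | −0.26 | +0.43 | 4.3% | 1.0% |
| 3% vs 10% | −0.63 | +0.98 | 8.3% | 0.3% |
| 6% vs 12% | −0.53 | +0.84 | 6.9% | 0.4% |

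**Oxygen duration**

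Assume three deaths after 1 to 3 oxygen days, survivors on oxygen averaging 7 to 10 days, and 5% to 40% of patients needing oxygen.

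- Against survivors who need oxygen: from 3 × (1 − 10)/50 = −0.54 to 3 × (3 − 7)/50 = −0.24 day. Always downward.
- Against the average patient: from 3 × (1 − 0.40 × 10)/50 = −0.18 to 3 × (3 − 0.05 × 7)/50 = +0.16 day. The sign is not fixed.

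**The case against.** The strongest reply is that the protocol gives only a label and a window. It does not say that the duration is raw or that death stops the clock. Scoring death at the maximum, or as a competing event, would be compatible with the text, and derivation rules of this kind are often left to an SAP, which is not at hand. This stands in part: an SAP could repair the point. But the protocol itself names the outcome and the test, and a plain duration under a t-test or rank-sum test has no natural place for death. The point is that a better variable is available, not merely that a rule is unwritten.

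A second reply is that harm would not be hidden. Mortality and need for mechanical ventilation are in the same list, death is the worst primary category, and fatal events are reported as serious. This also stands. It limits the consequence but does not correct the stay comparison.

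Three stronger readings are tempting and are not supported:

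- A reader might infer that both durations always turn death into benefit. For oxygen this fails. Entry requires room-air saturation above 94%, so many patients may have no oxygen days, and a patient who dies after two days of oxygen can then raise the arm mean.
- A reader might take (28 − 5)/50 = 0.46 day per death for stay, or (30 − 2)/50 = 0.56 day for oxygen, as the false benefit. These are gaps between two scoring rules, not the shift in the reported mean. For stay, that shift is 0.18 day under the central assumption.
- A reader might infer that oxygen duration will be compared only among patients who received oxygen. No section says so.

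**Conclusion.** The point holds for hospital stay. As written, an early in-hospital death counts as a short stay, against the ordering that the primary scale uses. The size is about 0.18 day per extra Day-5 death with 50 per arm and an assumed 14-day survivor mean, or 0.10 to 0.26 day over assumed means of 10 to 18 days. That is small, and deaths are likely to be few: the Background ratios suggest 3 to 7 in the whole trial, and the true number may be lower at ages 18 to 60 with good room-air saturation. What makes it worth correcting is the direction, since three extra deaths shift the mean by −0.54 day where worst-value scoring would shift it by +0.84.

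For oxygen duration the same flaw exists relative to survivors who need oxygen, but no consistent direction in the arm mean can be claimed. These are secondary outcomes, and the primary endpoint is unaffected.

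**What to change.** Replace the two durations by days alive and out of hospital to Day 28, and days alive and free of oxygen to Day 30. Analyse them in all randomized patients, with 0 for anyone who dies in the window, using the rank-sum test that the Statistical Methods section already lists. A discharge on Day 5 with no readmission then scores 28 − 5 = 23 days, and a death on Day 5 scores 0, which agrees with the primary scale. Patients who never need oxygen stay in the comparison. Report mortality beside both results, and give raw durations in survivors as description only.

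The change is to wording. It uses hospital dates, oxygen dates and vital status, which the existing outcomes already require. The cost is that the composite is slightly less direct to read than a duration.
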